**Sample size calculation**

To demonstrate an improvement of 5% in the active intervention group vs 1% in the control group in exercise tolerance (expressed in percentage exercise tolerance compared to what can be expected given the patient’s age and sex) would require 99 patients in the control group and 198 in the active intervention group (SD10%, alpha=0.05, power=0.90, ratio experimental to controls=2). Even if only 50% of patients in the experimental group adhere to the training, we would in the as-treated analysis compare three groups of each 99 patients, which would give us a power of 0.80. To account for non-adherence and loss to follow-up a total of 330 patients will be randomized. This number of patients will be sufficient to demonstrate a smaller difference (5% vs 2%) in a repeated measurements analysis with a power of 75-90% (2 follow-up measurements, correlation between follow up measurements=0.70, correlation between baseline & follow-up=0.50).

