# TREATMENT OF SUBJECTS

## Investigational product/treatment

Intervention:

The intervention is a mindfulness training and consists of a structured standardized online program, which has been provided to clients in the general population (http://www.psychologiemagazine.nl/web/Trainingen/Online-training-mindfulness.htm). Every 3 days the patient receives an email message with a link to a website where they are offered text explanations, video clips, sound tracks with mindfulness exercises, breathing exercises, assignments that need to be filled out, and practice suggestions for the coming few days. The online program is further supported by emails and intermittent text messages on the patient’s cell phone. The online training is currently 8 weeks. It will be extended to 12 weeks followed by reminder emails, sms-messages, and suggestions for continuing practice every 2-4 weeks thereafter until a year after the beginning. The low cost of the online programme (€ 30,-) gives the program the potential of being a cost effective intervention. Patients will not be charged for the online program. They will receive a personal code from Psychologie Magazine to start the online mindfulness training. Adherence to the intervention will be monitored by documenting whether the questions have been filled out.

In addition, all patients will receive usual care just like patients in the control group.

Control:

The control group will receive usual care which consists of regular outpatient visits, lifestyle advice regarding healthy nutrition, smoking cessation, physical activity, and stress reduction, and medical therapy and procedures if indicated.

Justification: See section 7.2

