# METHODS

## Study parameters/endpoints

### Main study parameter/endpoint

It is most likely that the mindfulness training will result in an improved quality of life. In this study we set out to search for an even more ambitious goal, and that is to find effects on physical variables. The 6 minute walk test has been chosen as primary outcome since it is a measure of cardiac and overall physical fitness. We expect that the mindfulness training will improve cardiac and overall physical fitness through the mindful breathing exercises, by encouraging a healthy lifestyle, and by reducing chronic anxiety and stress levels.

Primary outcome will be differences between the active intervention and control groups in the mean improvement at 3 months and 1 year, compared to baseline, of age- and sex expected exercise tolerance.

Exercise tolerance will be measured at baseline, 3 months and 1 year with the 6-minute-walk test (in which the distance is measured that a patient can walk within 6 minutes).

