### Other study parameters (if applicable)

We will document and adjust for baseline levels of traditional cardiovascular risk factors (blood pressure, smoking, lipids levels, body mass index), pre-existing anxiety and depression at baseline, and social economic status.
In the active intervention group we will monitor adherence to the online mindfulness training through the frequency of logging onto the website. In both active intervention and control group we will monitor participation in other mindfulness-based programs, practice of mindfulness-based exercises, and use of complementary care (through a modified Tic-P questionnaire).

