## Intention-to-treat and as-treated analysis

An intention-to-treat analysis will be performed to address whether offering mindfulness training is effective and cost-effective. Patients that are non-adherent to the offered training (cross-overs to usual care) will be analyzed as part of the active intervention group. Similarly, control patients who seek interventions on their own will be analyzed in the usual care group to which they were allocated.

An as-treated analysis will be performed to address whether mindfulness training is beneficial if actually performed and the treatment effect depending on the degree of adherence. The usual care group will consist of the control group. In the active intervention group, adherence to the intervention is monitored (see ‘’Intervention’’) and completion of sufficient number of training modules will be the criterion to determine which patients in the active intervention arm are included in the ‘’on-treatment’’ group. The ‘’on-treatment’’ group will consist of those patients who complete 50% or more of the exercises in the first 12 weeks. Patients who start the mindfulness training but complete less than 50% of the assignments in the first 12 weeks will be considered non-adherent and analyzed separately as the “partially treated’’ group. We will also evaluate outcome as function of the proportion of completed exercises as a continuous variable adjusting for potential confouders in a multivariable model. Finally, we will use the method developed by Robins and Tsiatis that corrects for non-compliance in randomized trials using rank preserving structural failure time models [25-26].

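### The only non-compliance correction named is a failure-time model, so for the walk test the effect of actually doing the training rests on non-randomised comparisons whose groups also leave out never-starters

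*Protocol*

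**What the plan says.** Protocol section 7.1.1 makes the primary outcome the between-arm difference "in the mean improvement at 3 months and 1 year, compared to baseline", on the walk test as a percentage of the expected value. This is a continuous measure. Section 9.3 plans survival analysis for one outcome only, the secondary composite clinical endpoint.

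Section 9.2 gives intention-to-treat the question of whether offering the training works. It gives the as-treated analysis the question of whether doing the training works. Three as-treated analyses are planned:

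- The whole control arm is compared with an on-treatment group (at least half of the exercises done in 12 weeks) and a partially treated group. The latter is defined thus: "Patients who start the mindfulness training but complete less than 50% of the assignments in the first 12 weeks will be considered non-adherent".
- Outcome is modelled on the proportion of exercises completed, adjusted for potential confounders.
- Last comes a method "that corrects for non-compliance in randomized trials using rank preserving structural failure time models". No outcome is attached to it.

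The sample size section plans "To demonstrate an improvement of 5% in the active intervention group vs 1% in the control group in exercise tolerance" with "SD10%, alpha=0.05, power=0.90, ratio experimental to controls=2", which "would require 99 patients in the control group and 198 in the active intervention group". It adds that at 50% adherence the as-treated analysis would compare three groups of 99 with power 0.80.

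**The concern.** Only the third analysis claims to deal with non-compliance in a way that uses the randomisation, and it needs event times. A change in walk distance, an SF-36 score or a hair cortisol level has none. For these outcomes the plan falls back on groups formed after randomisation by the patients' own behaviour. Adherence is counted over the 12 weeks that end at about the 3-month test, so a patient who is doing badly may stop training because of it.

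This is not a marginal analysis. The primary objective in section 2 concerns the effect of the training itself, and the effect of offering it is the secondary objective. The Summary describes the as-treated analysis alongside intention-to-treat under the main endpoint, and the sample size section gives it its own power. A positive on-treatment result could be read as evidence that the training improves walking when part or all of it reflects who chooses to persist.

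The group definitions also leave a gap. An active-arm patient who never starts is not on-treatment, is not partially treated, and cannot join usual care, which is limited to the control arm.

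**Working it through.** **Inputs from the sample size section:** difference 5 − 1 = 4 points, SD 10, alpha 0.05, 99 control and 198 active, 50% adherence, correlation 0.70 between follow-ups and 0.50 between baseline and follow-up. Sidedness is not stated; two-sided reproduces the plan, whereas one-sided would give 81 controls.

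**1. The plan's own figures.**
- Control n = (1.960 + 1.282)² × 10² × (1 + 1/2) / 4² = 98.5, rounded up to 99, with 198 active. Reproduced, with power 0.901.
- On-treatment vs control, 99 vs 99: SE = 10 × √(1/99 + 1/99) = 1.421; 4/1.421 = 2.81; power = Φ(2.81 − 1.96) = 0.80. Reproduced. The calculation assumes that the two groups would have the same mean without training.

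**2. What selection does to that test.** The documents give no selection size, so these are assumptions. If adherers would, untreated, improve g points more than non-adherers, then at 50% adherence they exceed the average patient, and hence the control arm, by 0.5g. With no true effect, no adjustment and SE 1.421:

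| g (adherers vs non-adherers) | Excess over average patient | Chance of rejection at nominal 5% |
|---|---|---|
| 0 | 0 | 5% |
| 2 | 1 | 10.8% |
| 4 | 2 | 29.1% |

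A simulation (2,000 trials per setting) gave 5.6%, 11.4% and 28.5%. With a true effect of 4 in adherers and none in others, the on-treatment difference averaged 3.9, 5.0 and 6.0. The intention-to-treat difference divided by the adherence proportion averaged 3.8, 4.0 and 3.9, and stayed within 0.1 of zero when there was no effect.

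**3. Price of a randomisation-based estimate.**
- Intention-to-treat SE, 99 vs 198: 10 × √(1/99 + 1/198) = 1.231.
- Divided by 0.5 adherence: 2.462. Half-width 1.96 × 2.462 = 4.8 points.
- Baseline-adjusted mean of two follow-ups: variance factor (1 + 0.70)/2 − 0.50² = 0.60. Half-width 4.83 × √0.60 = 3.7.
- On-treatment contrast for comparison: 1.96 × 1.421 = 2.8.
- The same 4.8 applies to a continuous dose, per full completion, if the mean proportion completed is 0.5.
- If adherers gain 4 and others nothing, the intention-to-treat difference is 2, with power 0.37 (99/198) or 0.40 (110/220, all 330 analysed). At 70% adherence it is 0.62 or 0.67.

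**4. The binary version has its own bias.** If half the active arm adheres and gains 4 while the other half gains 2, the intention-to-treat difference is 0.5 × 4 + 0.5 × 2 = 3. Dividing by 0.5 gives 6, against a true 4.

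**5. Never-starters.** Three groups of 99 use all 99 controls and all 198 active patients. That agrees with section 9.2 only if everyone starts. The protocol gives no rate of not starting. An assumed 5% to 30% would leave about 10 to 59 of the 198 in no group.

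**The case against.** The strongest reply is that the protocol never applies the failure-time model to the walk test. It attaches no outcome to it, and the composite endpoint is a legitimate use. A reader might infer that the plan runs a survival method on a continuous outcome; the text does not support that. What stands is narrower: the only correction named cannot serve the primary outcome.

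A reader might also infer that the on-treatment contrast is all that is left for the walk test. It is not. Section 9.2 also plans the dose-response model, in which never-starters could enter at zero, and section 9.4 adjusts for baseline risk factors. Both reduce measured confounding, but neither restores the randomised comparison.

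A third tempting reading is that adherence has competing definitions. Section 5.1 says "Adherence to the intervention will be monitored by documenting whether the questions have been filled out", and section 7.1.3 will "monitor adherence to the online mindfulness training through the frequency of logging onto the website". Only section 9.2 sets group membership, by share of exercises completed. Log-in frequency is monitoring, not a grouping rule, so conflicting memberships are not shown.

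The selection sizes are strong. The 29% case needs a 4-point gap between adherers and non-adherers, which is the trial's whole target effect; the 11% case needs half of it. Both are unadjusted. They show sensitivity and are not a forecast.

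Finally, an SAP that is not at hand may name a suitable estimator. But the protocol itself chose a correction and attached an unconditional power to the as-treated analysis, so the point concerns what it states and not detail it left open.

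**Conclusion.** The point holds in limited form. For the walk test and the other continuous outcomes, the protocol names no randomisation-based answer to whether the training works when done. The two analyses that remain are observational. The as-treated power of 0.80 is correct arithmetic, but it is conditional on equal prognosis of adherers and controls, which the protocol does not say. Under the assumed selection of 1 or 2 points above the average patient, at 50% adherence and unadjusted, false-positive rates are about 11% or 29%. Never-starters have no place in the as-treated groups, which conflicts with the three groups of 99. The intention-to-treat analysis, the sample size of 99 and 198, and the use of the failure-time model for the composite endpoint are not in question. This should be corrected, but it does not threaten the trial's randomised result.

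**What to change.** - State that the rank preserving model applies to the composite endpoint only.
- For continuous outcomes, add a randomisation-based estimate (two-stage least squares or a structural mean model). Use randomised arm as the instrument, proportion of exercises completed in 12 weeks as the dose with never-starters at zero, and the baseline value (for the primary outcome, the baseline walk test) as covariate. State the assumption that the effect is linear in dose.
- Report the binary complier effect (at least 50%) only as a sensitivity analysis. Say that it assumes no effect below 50% and overstates the effect if partially treated patients benefit.
- Say how mindfulness use among controls, which section 7.1.3 records, is handled in these estimates.
- Assign never-starters to a named as-treated group and reconcile this with the three groups of 99.
- Label the on-treatment versus control comparison exploratory, and its 0.80 power as conditional on equal prognosis.

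The cost is protocol or SAP wording and a little analysis work on data already collected. The real downside is statistical: further untestable assumptions, and an interval of about ±4.8 points at 50% adherence (±3.7 with baseline-adjusted repeated measures) against a 4-point target. The estimate may well be inconclusive, and the plan should say so in advance.

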## Univariable analysis

Short-term results (3 months) and mid-term results (1 year) will be calculated. Differences in mean improvements between the groups will be calculated for all outcome measures expressed on a continuous scale. Analysis with repeated measurement methods (mixed models) will be performed to account for multiple measurements performed during follow-up and for missing values.

Survival analysis will be performed with a failure being an event as defined according to the composite endpoint.

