### Secondary study parameters/endpoints

Key secondary outcome (measured at baseline, 3 months, 1 year):

- quality-of-life (SF36), using the mental- and physical composite outcome scales

Other secondary outcomes (measured at baseline, 3 months, 1 year):

- heart rate, blood pressure, resting respiratory rate (markers of cardiac fitness)
- NTproBNP (a biomarker for heart failure)
- cumulative cortisol in 2 cm of hair taken from the scalp (cumulative measure of stress)
- composite endpoint (all-cause mortality, heart failure, arrythmia, cardiac surgery, percutaneous cardiac intervention, electrical cardioversion)
- psychological well-being (Hospital Anxiety Depression questionnaire)
- preference values (societal EuroQol EQ-5D-5L values, societal SF-6D values obtained from the SF-36, VAS rating scale [Philip Moons version])
- Social support (perceived social support scale 12 Blumenthal PSSS12)
- Medical consumption of health-care use
- health care costs
- related non-health care costs (Tic-P)

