## Study procedures

At baseline, 3-months, and 1 year all patients will undergo exercise tolerance testing, measurement of heart rate, blood pressure and resting respiratory rate, cortisol measurement in 2 cm of scalp hair, and NTproBNP measurement and they will be asked to fill out questionnaires concerning quality-of-life, psychological well-being, medical resource use, and non-health care costs. Exercise tolerance will be measured with the 6-minute-walk test (in which the distance is measured that a patient can walk within 6 minutes).

NTproBNP will be determined in a blood sample. These samples will be coded in storage. Cumulative cortisol will be measured in 2 cm of one hair taken from the scalp. Clinical follow-up will provide data required for the composite endpoint.

Quality-of-life will be evaluated with the SF36. Psychological well-being will be determined with the Hospital Anxiety Depression Scale (HADS).

Preference values with be evaluated with the EuroQol EQ-5D-5L (societal values), the SF-6D from the SF-36 answers, and the VAS rating scale (patient values). Social support will be measured with the perceived social support scale 12 (PSSS12). Medical consumption will be measured with the Tic-P.Health care costs which will be determined on the basis of medical resource use multiplied by the actual or reimbursed costs per resource. Related non-health care costs will be determined using questionnaires (Tic-P) and will consist of the time costs for undergoing procedures, time costs for self-care including the mindfulness-training, the costs for support and care, costs for complementary care, and friction costs.

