## Economic Evaluation

If the 3 months and 1-year results indicate effectiveness of the mindfulness training, we will develop a Markov decision model to calculate long-term effectiveness, costs, and cost-effectiveness of offering mindfulness training to patients with structural heart disease. The comparison strategy will be usual care. We will perform the cost-effectiveness analysis from the health care and societal perspective considering a lifetime timeframe.

The model will consider different classes of heart failure, cardiovascular risk factors, cardiac events, quality of life, and costs. Event rates, risk factor changes, quality-of-life, health resource utilization, and cost data obtained from the clinical study will be integrated in the models. All co-investigators will be asked to review the model assumptions and inputs prior to performing the analysis in order to avoid bias. The economic evaluation will be performed in accordance with the Dutch recommendations for cost effectiveness analyses and we will explore UK and USA recommendations and costs in a sensitivity analysis.

Quality of life will be based on results from the trial where possible and where necessary from systematic reviews and Quality of Life catalogues available on the web. Costs that will be considered include direct medical costs (health-care costs for mind-body program, events, admissions, rehabilitation after an event, nursing home care for long-term disability), patient costs (out-of-pocket expenses for the mind-body program, time and travel costs associated with the program), and productivity losses (friction costs). Health-care costs will be estimated by multiplying health-care resource utilization with the cost per unit of resource. Future costs and life years will be discounted.

With the decision model we will calculate the effectiveness, the costs, the incremental cost-effectiveness ratios, the net health benefit, and the net monetary benefit for a number of willingness-to-pay thresholds. We will perform extensive (probabilistic) sensitivity analysis, threshold analysis, and value of information analysis.

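### Section 9.3 scores resource use and costs as change from baseline at a visit, which does not give the cost of the year after randomisation, and no rule adds the follow-up periods together

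*Protocol*

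**What the plan says.** Section 7.1.2 (Secondary study parameters/endpoints) gives one schedule for a mixed list: "Other secondary outcomes (measured at baseline, 3 months, 1 year". The list holds states such as heart rate and blood pressure, and also "Medical consumption of health-care use", health care costs, and "related non-health care costs (Tic-P").

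Section 9.3 (Univariable analysis) calculates a 3-month and a 1-year result and applies one rule: "Differences in mean improvements between the groups will be calculated for all outcome measures expressed on a continuous scale". It makes no exception for costs. It adds mixed models over the follow-up measurements. Section 7.1.1 shows what improvement means, because the primary outcome is the difference "in the mean improvement at 3 months and 1 year, compared to baseline, of age- and sex expected exercise tolerance".

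Section 7.3 (Study procedures) says health care costs are "determined on the basis of medical resource use multiplied by the actual or reimbursed costs per resource", and its non-health care costs include "time costs for self-care including the mindfulness-training". It names no period over which either is accumulated.

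Section 9.6 (Economic Evaluation) describes a lifetime Markov model with its own cost items, programme costs among them. The model is conditional on the 3-month and 1-year results indicating effectiveness. Its trial inputs are described as follows: "Event rates, risk factor changes, quality-of-life, health resource utilization, and cost data obtained from the clinical study will be integrated in the models".

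**The concern.** Blood pressure at 1 year minus blood pressure at baseline is a sensible measure of change. A cost is different: it is a total over an interval. A questionnaire at 1 year sees only its own look-back, and the baseline questionnaire sees a period before randomisation. Subtracting one from the other gives a change in spending between two windows, not what each arm cost during the trial year.

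Cost-effectiveness is part of the secondary objective (section 2), and section 9.2 assigns it to the intention-to-treat analysis. The course is the one cost that the design itself places in the active arm, and it comes at the start of follow-up. A 1-year contrast that does not reach back to the start would leave that cost out, along with any early difference in use of care.

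**Working it through.** **Inputs from the protocol.** Follow-up questionnaires at months 3 and 12 (section 7.1.2). Course of 12 weeks, price EUR 30 (section 5.1). Look-back R of the resource-use questionnaire: not stated, so a range is assumed. The protocol gives no figure for the cost outcomes that could be reproduced; its sample-size figures concern the walk test and do not enter here.

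**Timing.** 12 weeks = 84 days, and 3 months is about 365.25 / 4 = 91 days, so the course lies within months 0-3.

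**Formulas for a fixed look-back of R months (R up to 12).**
- Months of 0-3 inside the 1-year value: max(0, R - 9).
- Pre-randomisation months inside the 3-month value: max(0, R - 3).
- Follow-up months seen by the two questionnaires together: min(R, 3) + min(R, 9).

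| Look-back | 1-year value covers months | Months of 0-3 in it | Pre-randomisation months in 3-month value | Follow-up months seen, of 12 |
|---|---|---|---|---|
| 1 month | 11-12 | 0 | 0 | 1 + 1 = 2 |
| 3 months | 9-12 | 0 | 0 | 3 + 3 = 6 |
| 6 months | 6-12 | 0 | 3 | 3 + 6 = 9 |
| 9 months | 3-12 | 0 | 6 | 3 + 9 = 12 |
| 12 months | 0-12 | 3 | 9 | 3 + 9 = 12 |
| Since last visit | 3-12 | 0 | 0 | 3 + 9 = 12 |

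A correct 3-month value needs R = 3 and a correct 1-year value needs R = 12, so no single fixed R serves both. Reporting since the last visit sees the whole year once, but the 1-year value is then a 9-month total that needs the 3-month value added to it. The mixed model would also treat a 3-month total and a 9-month total as repeated measurements of the same quantity.

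**Which error matters.** Pre-randomisation months, and the baseline value that is subtracted, should balance between randomised arms in expectation. They change the meaning of each arm's figure and can add noise, but they do not by themselves bias the difference. Follow-up months that are never counted can.

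**Illustration.** Assume both arms spend EUR 100 a month, and the only difference is the EUR 30 price, placed in months 0-3 of the active arm. The true 12-month difference is EUR 30.
- R = 9: active 900 - 900 = 0; control 900 - 900 = 0; difference EUR 0. R = 1, 3 and 6 give EUR 0 in the same way.
- R = 12: active 1,230 - 1,200 = 30; control 1,200 - 1,200 = 0; difference EUR 30.

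**The case against.** The strongest reply is that section 9.3 is a general sentence and section 9.6 is where costs are really handled. Section 9.6 multiplies use by unit cost and lists the programme as well as the time and travel that go with it. The price is a known fixed amount and needs no patient recall. Months 0-3 are also reported at the 3-month visit and have their own result. Recall windows and the adding of questionnaire periods are commonly left to a statistical analysis plan, which is not shown here.

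Much of this stands, and it rules out several stronger readings that a reader might infer:

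- *That the 1-year result necessarily omits months 0-3.* This is so for a look-back of 9 months or less, or since the last visit. It is not so for 12 months, and the protocol does not say which applies.
- *That months 0-3 are lost to the trial.* The 3-month questionnaire captures them at least in part. What is missing is a rule that adds them.
- *That the training will look cheaper than it is in the economic evaluation.* The model counts programme costs.
- *That training time arises only in the active arm and only in months 0-3.* Section 5.1 encourages practice until a year after the start, and section 7.1.3 monitors mindfulness practice in both arms.
- *That a euro value can be put on the omitted training time.* The protocol gives neither a session length nor an hourly value. Section 5.1 implies 84 / 3 = 28 contacts, whereas section 10.4 implies 12 to 36 (1-3 a week for 12 weeks). The sample-size section allows for adherence as low as 50%. The EUR 30 price is the only programme cost figure in the document.

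Two things survive. The model is built only if effectiveness is indicated; otherwise section 9.3 is the only stated rule for the cost outcomes, and if the model is built it still draws on the trial's resource-use data. And the scoring rule is the protocol's own and covers all continuous outcomes, so an analysis plan that summed costs would depart from it.

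**Conclusion.** The point holds as a mismatch between a stated rule and the kind of quantity it is applied to. Read literally, sections 7.1.2 and 9.3 do not yield the cost of the 12 months after randomisation, and no section sums it. The size depends on the unstated look-back: the 1-year value contains 0 of the first 3 months for any look-back up to 9 months, and all 3 for a look-back of 12. In the illustration, the part that can be taken from the document is EUR 30 per active-arm patient, missed or counted accordingly. Any early difference in care use would be missed in the same way, by an amount the protocol does not allow one to estimate.

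The primary outcome and the key secondary outcome (SF-36) are unaffected. This is a low-severity point on secondary outcomes, worth considering because it is cheap to correct and because months that no questionnaire asks about cannot be recovered later, except from records.

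**What to change.** In section 9.3, exempt resource use and costs from the improvement rule. Define the 1-year outcome as the cumulative total from randomisation to 12 months (months 0-3 plus months 3-12), and compare these totals between the randomised arms. Add the known programme price, and count reported training time in whichever period it occurs. Use the baseline value only as a covariate.

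In section 7.3, or in the analysis plan if it already covers this, check that the recall periods of the two follow-up questionnaires, supplemented by hospital records, together cover months 0-12 without counting pre-randomisation months.

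The cost is a short addition to section 9.3 and possibly a changed recall heading on a questionnaire that section 7.1.3 already describes as modified. No extra visits or patients are needed. The drawback is some added recall error for self-reported items over the longer interval, which hospital records offset only in part.

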## Multivariable analysis

Multivariable analysis will be performed to adjust for any chance differences in risk factors at baseline that can clinically be expected to affect the outcome, for congenital heart disease vs cardiomyopathy, and for socio-economic status and to test for interaction effects. Furthermore, we will test for a differential effect on outcome depending on the level of pre-existing anxiety and depression.

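### Sections 9.3 and 9.4 leave the precision gain from baseline adjustment unsecured: the outcome's own baseline is in no adjustment list, and covariates are chosen by observed imbalance

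*Protocol*

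**What the plan says.** Section 7.1.1 defines the primary outcome as the between-group difference in mean improvement from baseline in the 6-minute walk test, as a percentage of what age and sex predict, at 3 months and 1 year. Section 9.3 carries this into the analysis: "Differences in mean improvements between the groups will be calculated for all outcome measures expressed on a continuous scale". Its next sentence plans repeated-measurement mixed models to handle the several follow-up measurements and missing values. It does not say whether the baseline value is a covariate, part of the outcome vector, or absent.

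Two places deal with adjustment:

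- Section 7.1.3: "We will document and adjust for baseline levels of traditional cardiovascular risk factors" (blood pressure, smoking, lipids, body mass index), and also pre-existing anxiety and depression and socio-economic status.
- Section 9.4: "Multivariable analysis will be performed to adjust for any chance differences in risk factors at baseline that can clinically be expected to affect the outcome". It adds diagnosis (congenital heart disease or cardiomyopathy), socio-economic status and interaction tests.

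Neither names the baseline walk test, nor the baseline value of each outcome as a general rule. Section 7.3 has the walk test done at baseline in all patients.

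After the main calculation, the sample size section claims 75-90% power for a smaller difference (5% vs 2%) in a repeated-measurements analysis with two follow-ups, assuming "correlation between follow up measurements=0.70, correlation between baseline & follow-up=0.50". It does not say which analysis belongs to which end of that range.

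**The concern.** At a baseline/follow-up correlation of 0.50, subtracting the baseline gains nothing over analysing follow-up alone, whereas adjusting for it removes a quarter of the single-measurement variance. The baseline of the outcome is also the only candidate covariate whose correlation with the outcome the protocol quantifies, yet it is missing from both lists. The sample size section therefore quotes a range whose top needs an analysis that the statistics section does not commit to.

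The covariate rule in Section 9.4 raises a second, smaller issue. It adjusts for risk factors that happen to differ between the arms. Section 9.1 says that no formal tests of baseline differences will be done, so imbalance would be judged by eye with no stated criterion. The adjusted estimate then depends on a choice made after seeing the baseline data. Section 7.1.3 reads as an unconditional commitment to a named set, which is a different rule.

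**Working it through.** **Inputs, all from the sample size section.** "To demonstrate an improvement of 5% in the active intervention group vs 1% in the control group in exercise tolerance" is a difference of 4 points. Further: "SD10%, alpha=0.05, power=0.90, ratio experimental to controls=2". Sidedness is not stated; two-sided is assumed because it reproduces the sample size. Group sizes: "99 patients in the control group and 198 in the active intervention group", 297 in total. The 330 randomised patients split 110 and 220 at 2:1. The smaller difference is 3 points, with two follow-ups and correlations 0.70 and 0.50.

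**Step 1: reproduce the main sample size.** Control n = (1 + 1/2) × (1.96 + 1.2816)² × 10² / 4² = 1.5 × 10.51 × 6.25 = 98.5, so 99, with 198 in the intervention arm. The plan's figure is reproduced; the power is 90.1%.

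**Step 2: variance factors for the mean of two follow-ups**, relative to SD² = 100 and assuming equal variances at each visit:

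- Follow-up only: (1 + 0.70)/2 = 0.85
- Change from baseline: 0.85 + 1 − 2 × 0.50 = 0.85
- Baseline as covariate: 0.85 − 0.50² = 0.60

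**Step 3: power for 3 points.** Power = Φ(3 / [10 × √f × √(1/n_c + 1/n_t)] − 1.96).

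- At 99/198, √(1/99 + 1/198) = 0.1231. With f = 0.85 the standard error is 1.135 and power is Φ(2.64 − 1.96) = 75.3%. With f = 0.60 it is 0.953 and power is Φ(3.15 − 1.96) = 88.2%.
- At 110/220, √(1/110 + 1/220) = 0.1168. The standard errors are 1.077 and 0.905.

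| Analysis | f | 297 patients | 330 patients |
|---|---|---|---|
| Follow-up only | 0.85 | 75.3% | 79.6% |
| Change from baseline | 0.85 | 75.3% | 79.6% |
| Baseline as covariate | 0.60 | 88.2% | 91.3% |

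At 297 patients the results lie within 2 points of both ends of the stated 75-90%. At 330 the lower end does not fit. The variance reduction is 1 − 0.60/0.85 = 29%. Without adjustment, the same power needs 0.85/0.60 = 1.42 times as many patients.

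**Step 4: does this touch the main design?** No. For a single follow-up the change score has factor 2 − 2 × 0.50 = 1.00, so its SD is the planned 10 and power for 4 points is the planned 90%. With two follow-ups, even the change score gives 94.1% at 99/198.

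**Step 5: sensitivity to the baseline correlation** (297 patients, 3 points, 0.70 between follow-ups):

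| Baseline correlation | Follow-up only | Change | Baseline as covariate |
|---|---|---|---|
| 0.30 | 75.3% | 58.7% | 79.8% |
| 0.50 | 75.3% | 75.3% | 88.2% |
| 0.70 | 75.3% | 95.3% | 98.2% |

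Adjustment is the best of the three at each value; the size of the gain depends on the correlation.

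**The case against.** A reader might infer that the trial will run the weaker analysis and so gives up the gain. The protocol does not support that. The mixed model in Section 9.3 would recover the whole gain if baseline were a covariate or if the baseline mean were constrained equal across arms. Only a model with free baseline means per arm, or one that ignores baseline, would match the 0.85 factor. The protocol names none of these and nowhere excludes the baseline as covariate. A difference in mean improvement is also an effect measure: regressing change on arm and baseline gives the same treatment estimate as regressing follow-up on arm and baseline. Such model detail is often left to a statistical analysis plan, and one may exist that is not shown here. All of this stands, so the gain is unsecured, not lost.

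A reader might also infer that 75% is the change-score analysis and 90% the baseline-adjusted one. The document does not say so, and follow-up-only analysis gives 75% as well. If the sponsor did derive the upper end from a baseline-adjusted model, that suggests it had this analysis in view.

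Nor is the trial underpowered on this account: its sample size rests on 5% vs 1%, and the range stated for 5% vs 2% already includes the unadjusted 75%.

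On covariates, Sections 7.1.3 and 9.4 can be read together, with the former supplying the candidates and the latter limiting them to clinically relevant ones. That softens the inconsistency but leaves selection by imbalance in place. It concerns the additional multivariable analysis, not the comparison in Section 9.3. The power argument supports only the outcome's own baseline, so it gives no ground for putting the whole Section 7.1.3 list into the main model.

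**Conclusion.** The point holds as a free improvement. The protocol's wording allows analyses of the 5% vs 2% difference whose power differs by about 12 to 13 percentage points (88.2 − 75.3 = 12.9 at 297 patients; 91.3 − 79.6 = 11.7 at 330), and it does not commit to the better one. The figures assume a two-sided 0.05 test, SD 10 at each visit, the protocol's two correlations, and an effect averaged over both follow-ups. The 90% power for 5% vs 1% is intact. Separately, choosing covariates by observed imbalance is a weak rule as stated, and its relation to Section 7.1.3 should be settled before the data are seen.

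**What to change.** In Section 9.3, state that the main intention-to-treat mixed model of the 3-month and 1-year values includes the outcome's own baseline as covariate, or constrains the baseline mean to be equal across arms. Apply this to the walk test and to each continuous secondary outcome. The treatment effect remains the difference in mean improvement.

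In Section 9.4, replace adjustment for chance differences with one pre-specified covariate list, reconciled with Section 7.1.3, for use in the additional multivariable analysis.

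It would also help if the sample size section said which analysis and which number of patients lie behind each end of the 75-90% range. The cost is a few sentences; no new data, visits or patients are needed.
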